## Abstract

**Background:**

Insomnia is a common sleep disorder that affects many adults either transiently or chronically. The societal cost of insomnia is on the rise, while long-term use of current drug treatments can involve adverse effects. Recently, electroacupuncture (EA) has been used to treat various conditions including insomnia. The objective of this study is to provide scientific evidence for the effect and safety of using EA to treat insomnia.

**Methods/design:**

In this multicentre, assessor-blind, three-arm, parallel-design, randomised controlled trial, 150 participants will be assigned to the EA group, the sham EA (SEA) group, or the usual care group. The EA and SEA groups will receive the specific treatments 2–3 times a week for 4 weeks, for a total of 10 sessions, whereas the usual care group will not receive EA and will continue with usual care during the same time period. The primary outcome measure will be changes in the Insomnia Severity Index 5 weeks after randomisation. The secondary outcomes will include the Pittsburgh Sleep Quality Index, the Hospital Anxiety and Depression Scale, a sleep diary, the EuroQoL-5 dimension questionnaire, the levels of melatonin and cortisol, and the Patient Global Impression of Change. Safety will be assessed at each visit.

**Discussion:**

The results of this multicentre randomised controlled trial will contribute to provide rigorous clinical evidence for the effects and safety of EA for insomnia disorder.

**Trial registration:**

Korean Clinical Trial Registry, CRIS, KCT0001685. Registered on 2 November 2015 (retrospectively registered). Date of enrolment of the first participant to the trial 13 October 2015.

**Electronic supplementary material:**

The online version of this article (doi:10.1186/s13063-017-1922-7) contains supplementary material, which is available to authorized users.

## Background

Insomnia is one of the most common sleep disorders and is defined as a condition in which the patient experiences sleep disturbances accompanied by daytime symptoms or is unable to sleep despite having adequate circumstances and opportunities for sleep [1]. Approximately 40% of adults have experienced some form of insomnia, with chronic insomnia affecting approximately 10–15% of those individuals [2]. According to the Diagnostic and Statistical Manual of Mental Disorders, fifth edition (DSM-5), the diagnostic criteria for insomnia includes difficulty initiating and maintaining sleep, early awakening, and having sleep difficulties at least three times a week and lasting at least 3 months [3]. Furthermore, insomnia refers to a sleep disorder that is not caused by medications, pain, a physical disease, depressive disorder, or other psychiatric illnesses. Insomnia includes not only an inability to fall asleep at night but also an impairment of daytime activities and functioning (i.e. fatigue, nervousness, and a reduction in motivation or energy) with poor concentration, headache, and diminished quality of life [4].

The economic costs associated with insomnia are significant. In the USA, approximately 30–35 billion dollars are spent each year on insomnia, with more than $1253 being spent by the average adult directly and indirectly to manage the condition [5]. Furthermore, given that insomnia is closely linked to depression, anxiety disorders, alcohol or drug abuse/dependence, and suicide, it requires continuous management and treatment beginning in its early stages [6].

Currently, insomnia is most often treated with pharmacological therapy, such as benzodiazepines, and cognitive behavioural therapy. However, while drug treatment can be effective for the short-term management of insomnia, there is little evidence whether efficacy is maintained in the long term, and adverse effects, including feelings of weakness during the daytime, mental slowing, dizziness, sensitivity to light, decreased exercise capacity, and dependency, have been linked to long-term use of these pharmacological agents [7, 8]. Moreover, although randomised controlled trials have reported the efficacy of cognitive behavioural therapy, few therapists are well-trained in this technique for it to be widely used, and there are no clear standardized guidelines about the optimal number and duration of treatments for insomnia [1]. Consequently, treatments for insomnia based on complementary and alternative medicine have received increasing attention.

Acupuncture is now in widespread use, and has been applied for the treatment of various sleep disorders. Recently, several published clinical studies and systematic reviews have shown its use to treat insomnia [9]. According to a systematic review by Yeung et al. [10], 20 randomised clinical trials concluded that acupuncture is more effective than benzodiazepines for the treatment of insomnia; however, these studies have several limitations, including the eligibility criteria used, randomisation, blinding, and small sample sizes. Although several studies have also demonstrated that acupuncture and electroacupuncture (EA) can be effective for treating insomnia [11, 12], poor methodological quality in these studies resulted in a low level of evidence [13]. There have been few multicentre reports on the use of EA for insomnia, and large-scale studies on the efficacy and safety of acupuncture and EA to treat insomnia are necessary. Therefore, the present study aims to provide objective evidence of the effect and safety of EA for insomnia.

## Methods/design

### Study design and setting

We designed a multicentre, randomised, assessor-blind, controlled, parallel-group study to compare the effect and safety of EA, sham electroacupuncture (SEA), and usual care in subjects with insomnia. The participants will be recruited using regional newspapers, flyers, advertisement boards, etc. Potential candidates for the study will be screened and fully informed about the study. Eligible participants will be randomly assigned to three groups and receive treatment for 4 weeks with 2 months of follow-up. The study flow chart is shown in Fig. 1. The Standard Protocol Items: Recommendations for Interventional Trials (SPIRIT) checklist and figure are given in Additional file 1 and Fig. 2, respectively.

**Fig. 1 Fig1:**
[figure not shown]
Study flow chart

**Fig. 2 Fig2:**
[figure not shown]
The SPIRIT figure. The schedule of enrolment, interventions, and assessments. *EA* electroacupuncture, *EQ-5D* EuroQoL five dimension questionnaire, *HADS* Hospital Anxiety and Depression Scale, *ISI* Insomnia Severity Index, *PGIC* Patient Global Impression of Change, *PSQI* Pittsburgh Sleep Quality Index

An independent researcher that is blinded to the group allocation will perform the outcome assessment and statistical analysis.

### Study population

#### Inclusion criteria

Candidates who meet the following criteria will be included:age 19–64 years;an Insomnia Severity Index (ISI) score ≥15 points;fulfilment of the DSM-5 diagnostic criteria for insomnia disorder; andwillingness to sign an informed consent.

#### Exclusion criteria

Individuals meeting any of the following criteria will be excluded:a diagnosis of major depressive disorder, anxiety disorder, panic disorder, or other psychiatric disorders; caffeine, alcohol, or drug addiction; or a Hospital Anxiety and Depression Scale (HADS) score ≥11 points;working shifts or changes in day/night work schedule that could impact circadian rhythm;suffering from pain severe enough to cause sleep disturbance or presence of any disease that could cause insomnia;having undergone any therapy or taken any medication as required in the previous 2 weeks, or a change in the type or dosage of a regularly taken medication in the previous 4 weeks to alleviate insomnia;taking medication for a cardiovascular or haemostatic disorder;a diagnosed unregulated hormone disorder, serious or systemic disease (e.g. hyperthyroidism, chronic liver disease or chronic kidney disease) that could affect sleep;a previous hypersensitivity reaction to acupuncture or difficulty co-operating with acupuncture therapy;the presence of implants that could interfere with EA or a history of hypersensitivity to electrostimulation;pregnancy, lactation, or planning a pregnancy; anddifficulty complying with the treatment, questionnaire, or study protocol

### Randomisation, allocation concealment, and blinding

Subjects who meet the eligibility criteria will be randomly allocated to one of three groups in a 1:1:1 ratio through stratified block randomisation based on whether medications are taken to treat insomnia and the institutions conducting the trial. An independent statistician ([name]) will use SAS® version 9.4 software (SAS Institute Inc., Cary, NC, USA) to generate random assignment tables. The randomisation list will be sealed in sequentially numbered opaque envelopes and delivered to each institution, where they will be stored in a double-locked cabinet. Only the practitioners will be aware of the group allocation of each patient. After random assignment, the envelope will again be stored separately in a double-locked cabinet. Allocation concealment will not be broken until the trial is complete. Since it would be impossible to blind the practitioners, they will not be involved in the assessment. The outcome assessors and data analysts will be blinded to the group allocation.

### Interventions

The EA group will be treated with 0.25 × 40 mm disposable sterilized filiform needles (Dong-bang Acupuncture Inc., Seoul, Korea) applied to the Baihui (GV20), Yintang (EX-HN3), bilateral Shenmen (HT7), Neiguan (PC6), Jinmen (BL63), and Dazhong (KI4) acupoints by inserting and manipulating the needle to achieve *de qi* (2–3 times a week for 4 weeks, for a total of 10 sessions). After *de qi* is achieved, an EA device (ES-160, Ito Co. Ltd., Tokyo, Japan) will be used to apply 4 Hz for 30 min at 80% intensity of the stimulation felt by the participant.

For the SEA group, a Park Sham Device (PSD; Dong-Bang AcuPrime Ltd., Exeter, UK) will be used to needle 10 specific non-acupoints on both the arms and legs during the same period using the same needling schedule as the EA group. The PSD is one of many sham acupuncture methods used in acupuncture studies [14, 15]. It has a blunt end that retracts to shorten the length of the needle and give the appearance that needling will be performed without the needle actually penetrating the skin. Electrostimulation in the SEA group will be performed using the same EA device (ES-160) that is used in the EA group. The de-activated device will be connected to the PSD and applied for 30 min, while making the same beeping sound and light indicators when operated without delivering any electrostimulation.

The EA and SEA groups will be prohibited from undergoing any additional treatments for insomnia during the study period. The planned acupuncture treatment is based on Standards for Reporting Interventions in Clinical Trials of Acupuncture (STRICTA) and Consolidated Standards of Reporting Trials (CONSORT), and detailed information is summarized in Table 1.

**Table 1 Tab1:** Details of acupuncture treatment based on the revised STRICTA checklist

	Item	Detail
1. Acupuncture Rationale	1a) Style of acupuncture	EA based on traditional medicine theory
	1b) Reasoning for treatment provided, based on historical context, literature sources, and/or consensus methods, with references where appropriate	Textbook on acupuncture and Moxibustion, related literature [10–12, 43], consensus by experts in acupuncture and insomnia
	1c) Extent to which treatment was varied	Standardized treatment
2. Details of acupuncture	2a) Number of needle insertions per subject per session	Fixed 10 acupoints
	2b) Names of points used	EA treatment group: Unilateral GV20, EX-HN3, bilateral HT7, PC6, BL63, KI4
	2c) Depth of insertion	From 5 to 20 mm
	2d) Response sought	*de qi* during needling and perception of stimulus during electrostimulation
	2e) Needle stimulation	After manual stimulation, 4 Hz will be conducted and stimulation will be at 80% intensity of the stimulus the participant perceives
	2f) Needle retention time	30 min
	2 g) Needle type	0.25 × 40 mm sterilized stainless steel needle
3. Treatment regimen	3a) Number of treatment sessions	Total 10 sessions
	3b) Frequency and duration of treatment sessions	2–3 sessions per week for 4 weeks
4. Other components of treatment	4a) Details of other interventions administered to the acupuncture group	All three groups will be educated through sleep hygiene brochure. Usual care group will be permitted to have any type of treatment
	4b) Setting and context of treatment, including instructions to practitioners, and information and explanations to patients	The practitioner will limit unnecessary conversation that does not pertain to the treatment or patient
5. Practitioner background	Description of participating acupuncturists	Korean Medical Doctors who have a license and at least 2 years of clinical experience
6. Control or comparator intervention	6a) Rationale for the control or comparator in the context of the research question, with sources that justify this choice	Park sham placebo device will be used as a sham control [12, 14]
	6b) Precise description of the control or comparator. If sham acupuncture or any other type of acupuncture-like control is used, provide details as for items 1–3 above.	SEA control group: use Park sham placebo device on 10 non-acupoints on both upper and lower limb and connect the electrostimulator in switch-off state for removal after 30 min

*EA* electroacupuncture, *STRICTA* Standards for Reporting Interventions in Clinical Trials of Acupuncture

The usual care group will be allowed to undergo any treatment for insomnia except traditional medicine such as acupuncture, moxibustion, and herbal treatment. The participants will be asked to inform the research investigators of any new treatments received after entry into the trial, and all concomitant treatments will be recorded on the case report form (CRF). All three study groups will be educated using a brochure on sleep hygiene.

### Sample size

The objective of this clinical trial is to conduct a comparative analysis on the effect and safety of EA for treating patients with insomnia. We used data from two previous studies [11, 12] to estimate the difference in the mean ISI values for the EA treatment and SEA control groups as 4.15, and the standard deviation as 6.0. Then the sample size was calculated using a two-sided 2.5% significance level and 80% statistical power. Moreover, the usual care group will require a smaller sample size because differences in the ISI before and after treatment are expected to be larger between the EA and usual care groups than between the EA and SEA groups; therefore, this trial will assign participants to the three groups in a 1:1:1 ratio. Each group will have a minimum of 40 participants for a total of 120 participants, which will allow for a dropout rate of 20%, thus requiring a minimum of 150 participants.

### Outcome measures

#### Primary outcome

The primary outcome measure in this study is ISI, which is a seven-item questionnaire designed to determine the diagnosis and degree of insomnia. The reliability and validity of this questionnaire is well established [16], and the validated Korean version of the ISI will be used in this study [17]. The total score of the ISI ranges from 0 to 28 points, and the participants will be classified as follows: no clinically significant insomnia (0–7 points), subthreshold insomnia (8–14 points), clinical insomnia of moderate severity (15–21 points), and severe clinical insomnia (22–28 points) [17].

#### Secondary outcomes

Sleep quality will be assessed using the Pittsburgh Sleep Quality Index (PSQI) questionnaire. The PSQI is an instrument that assesses sleep quality and disturbance within the past month by measuring seven categories: subjective sleep quality, sleep latency, sleep duration, habitual sleep efficiency, sleep disturbances, use of sleeping medication, and daytime dysfunction. The PSQI has been shown to be highly consistent with sleep diary and polysomnography (PSG) results in patients with primary insomnia, and is recommended as an assessment tool in patients who are suspected of having insomnia [18, 19].

Sleep diaries, which are a daily record on the patient’s sleep, are widely used to collect direct information on sleep and waking patterns in patients with insomnia [20]. In this study, the sleep diary will contain details on when the participant went to bed at night, waking time in the morning, sleep latency, the number of times and duration the participant woke during the night, whether daytime naps were taken, and whether the participant used sleeping aids.

The HADS consists of 14 items with seven odd-numbered anxiety subscales (HADS-A) and seven even-numbered depression subscales (HADS-D). This questionnaire is a validated and reliable psychological instrument that is widely used to assess changes in emotional state, such as anxiety and depression, in patients with chronic diseases. Assessment will be performed using a four-point scale (0–3 points), with higher scores indicating more severe symptoms. Zigmond and Snaith grouped each subscale as follows: non-cases (0–7 points), doubtful cases (8–10 points), and cases (11–21 points) [21]. A previous standardization study reported the sensitivity and specificity of the Korean versions of the HADS-A and HADS-D [22].

To observe physiological changes in the patient, the levels of salivary melatonin and cortisol will be assessed. Melatonin is secreted from the pineal gland and has a direct effect on sleep structure [23]. Cortisol is produced in the adrenal cortex and its secretion is regulated by the hypothalamic-pituitary-adrenal axis. Studies have shown that changes in cortisol concentrations are associated with stress and sleep [24]. Because both melatonin and cortisol concentrations can fluctuate according to a circadian rhythm, the samples will be collected and analysed after scheduling the participant visit and conducting educational sessions on the use of the saliva collection kit in advance [25].

The EuroQoL five dimension questionnaire (EQ-5D) will be used to measure health-related quality of life. This instrument is designed to have the subject check the most appropriate response to five items on health status; each checked item will have a weighted score of 1, 2, or 3, and the combination of the five numbers will represent the health status of the subject [26]. In addition, the EQ-5D and ISI will be used to estimate the parameters needed for economic evaluation. The Patient Global Impression of Change (PGIC) will be used to assess the participant’s subjective perception of overall improvement after treatment.

The time points for each assessment and the procedures are summarized in Table 2.

**Table 2 Tab2:** Schedule for treatment and outcome assessment

Visit	Screening	1	2–5	6	7–10	11	12	13
Week		1	1–2	3	3–4	5	9	13
Informed consent	●							
Inclusion/exclusion criteria	●							
Treatment expectation questionnaire	●							
Vital signs	●	●	○	●	○	●	●	●
Demographic characteristics	●							
Medical history	●							
Laboratory tests	●					●		
Random allocation		●						
Change of medical history		●	○	●	○	●	●	●
EA treatment		○	○	○	○			
ISI	●	●		●		●	●	●
Melatonin/cortisol study		●				●		
PSQI		●		●		●	●	●
Sleep diary	●	●		●		●	●	●
HADS	●	●		●		●	●	●
EQ-5D		●		●		●	●	●
PGIC				●		●	●	●
Blinding test		○			○			
Safety assessment		●	○	●	○	●	●	●

●, All groups; ○, treatment groups

*EA* electroacupuncture, *EQ-5D* EuroQoL five dimension questionnaire, *HADS* Hospital Anxiety and Depression Scale, *ISI* Insomnia Severity Index, *PGIC* Patient Global Impression of Change, *PSQI* Pittsburgh Sleep Quality Index

### Statistical analysis

The primary outcome measure in this study is the mean change in the ISI from baseline to week 5. A two-sided test with a significance level of 0.025 will be performed using an analysis of covariance with baseline as the covariate and the treatment group as the fixed factors. The intra-group ISI changes from baseline to post-treatment will be analysed using Student’s paired *t* test or Wilcoxon signed-rank test, and reported with a 95% confidence interval. In addition, we will use a repeated-measures analysis of variance to identify any trend changes. Dunnett’s test will be used for inter-group comparisons to compensate for multiple comparisons.

The methods used to analyse the secondary outcome measures, i.e. ISI at weeks 3, 9, and 13, PSQI, HADS, EQ-5D, PGIC, changes in sleep diary entries, and changes in melatonin and cortisol levels, will be the same as those used for the primary assessment analyses. The chi-square test or Fisher’s exact test will be used for categorical data. Analyses will be conducted on an intent-to-treat basis, and multiple imputations will be applied if there are missing values.

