There are limitations to this study. First, we will perform sham electroacupuncture using a sham EA device and PSD as a control intervention in the SEA group. However, the currently developed sham acupuncture interventions are not completely inert physiologically, and previous studies reported that sham acupuncture interventions not only have some physiological activity, but could also be associated with larger effects than pharmacological and other physical placebos [39–41]. Placebo effects are very commonly observed and should be controlled appropriately in sleep disorder clinical trials [42]. Therefore, we will apply the non-penetrating placebo device at non-acupoints to minimize this bias, and we will also include a usual care group as a control. Second, although PSG is generally considered the gold standard in sleep studies, it is not always included in actual clinical trials due to its costs, burden on patients, and research conditions. In the present multicentre trial, PSG is not feasible and various outcome measures including a sleep diary, ISI, PSQI, HADS, melatonin and cortisol will be assessed. We will evaluate objective sleep parameters such as PSG or actigraphy in future studies. In spite of its limitations, the results of this multicentre randomised controlled trial may provide rigorous evidence for a multi-faceted evaluation of the effect and safety of EA for treating insomnia.

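### The primary analysis does not make electroacupuncture versus sham, the only contrast the trial is sized on, the comparison that decides the trial

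*Protocol article*

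**What the plan says.** All places are in the protocol article.

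- **Endpoint** (Statistical analysis): "The primary outcome measure in this study is the mean change in the ISI from baseline to week 5".
- **Primary test** (same section): "A two-sided test with a significance level of 0.025 will be performed using an analysis of covariance". The model adjusts for the baseline score and enters treatment group as a factor. No pair of arms is named.
- **Multiplicity** (same section): after a sentence on repeated-measures ANOVA comes "Dunnett’s test will be used for inter-group comparisons to compensate for multiple comparisons". The reference arm and the family-wise level are not given. The same methods are then applied to the secondary outcomes.
- **Sizing** (Sample size): the authors used two earlier studies "to estimate the difference in the mean ISI values for the EA treatment and SEA control groups as 4.15", with SD 6.0, two-sided 2.5% and 80% power. They expect a larger difference for EA against usual care but give no figure for it.
- **Role of usual care** (Discussion): because sham needling may not be inert, "we will also include a usual care group as a control". SEA is also called a control, in the same paragraph and in Table 1.
- **Blinding** (Randomisation, allocation concealment, and blinding): "Only the practitioners will be aware of the group allocation of each patient". Usual care participants receive neither EA nor sham, and Table 2 gives the blinding test to the two treatment groups only.

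**The concern.** In a three-arm trial, the test of the group factor in an ANCOVA has 2 degrees of freedom and asks whether any arm differs from any other. That is not the question the trial was sized to answer. Dunnett's test compares several arms with one reference, so it is undefined until the reference is named:

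| Reference | Comparisons made | Comparison left out |
|---|---|---|
| Usual care | EA–usual care, SEA–usual care | EA–SEA |
| SEA | EA–SEA, SEA–usual care | EA–usual care |
| EA | EA–SEA, EA–usual care | SEA–usual care |

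Only EA as reference gives the two contrasts that the Sample size section discusses.

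EA versus SEA is the only comparison involving EA that is designed to blind participants and match their contact with practitioners. EA versus usual care is open-label and scored by questionnaire. The usual care arm may also take other insomnia treatments that are barred in the other two arms. Expectation and attention effects common to EA and SEA could therefore produce a positive primary test with no effect of EA over sham.

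There is also the level. A value of 0.025 looks like 0.05 already divided over two comparisons, yet Dunnett is added to compensate for multiplicity.

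**Working it through.** **Inputs from the Sample size section.** EA–SEA difference 4.15, SD 6.0, two-sided 0.025, power 80%, 40 evaluable per arm, 20% dropout. **Assumed.** Usual care deficits of 2 to 6 points, since the article gives none. SD 6.0 is used throughout, with no gain from the baseline covariate.

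**1. The plan's own figure.** n per arm = 2(z₀.₉₈₇₅ + z₀.₈₀)² SD² / δ² = 2(2.241 + 0.842)² × 36 / 4.15² ≈ 39.7, so 40. Then 120 / (1 − 0.20) = 150. Both reproduce. Power at n = 40 is 80.3% by the normal formula and 78.9% by the two-sample t test. The sized question is therefore EA versus SEA at two-sided 0.025.

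**2. The three-group test when EA equals SEA.** If usual care is worse by d, the noncentrality is λ = n × (2/3)d² / SD² = 40 × (2/3)d² / 36. The test is F with 2 and 116 df (120 − 3 arms − 1 covariate) at 0.025.

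| d (points, assumed) | λ | P(positive test) |
|---|---|---|
| 2 | 2.96 | 22% |
| 3 | 6.67 | 51% |
| 4.15 | 12.76 | 83% |
| 5 | 18.52 | 95% |
| 6 | 26.67 | 99% |

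The effect of EA over sham is zero in every row.

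**3. Dunnett together with 0.025.** With two comparisons and equal arms (correlation 0.5, 116 df), critical values were found by simulation of 4,000,000 draws. The standard error of a contrast is 6√(2/40) = 1.342, so the noncentrality for EA–SEA is 4.15 / 1.342 = 3.09.

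| Rule | Critical value | Per-comparison level | EA–SEA power, n = 40 |
|---|---|---|---|
| Two contrasts at 0.025 each, no Dunnett | 2.27 | 0.025 | 79.3% |
| Dunnett, family-wise 0.05 | 2.24 | 0.027 | 80.2% |
| Dunnett, family-wise 0.025 | 2.52 | 0.013 | 71.7% |

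The first rule has a family-wise error of about 0.046. The last would need 48 evaluable per arm for 80% power: 48 / 0.8 = 60 randomised per arm, 180 in all.

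**4. Is naming the Dunnett reference enough?** With EA as reference, family-wise 0.025 and EA equal to SEA, the EA–usual care comparison alone is significant 16%, 39%, 72% and 88% of the time for deficits of 2, 3, 4.15 and 5 points. The plan must also say which contrast carries the efficacy claim.

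**The case against.** The article never calls the primary test omnibus, overall or global. Treatment group as a factor is also how one sets up an ANCOVA that yields pairwise contrasts. Two-sided fits a pairwise contrast and does not fit a 2-df F test, and the level matches the one used to size EA versus SEA. The only pairs discussed under Sample size have EA in common, so the intended Dunnett reference can be guessed. A condensed article may leave the contrast statement to the analysis plan.

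Much of this stands, and it rules out two stronger readings. A reader might infer that the plan prescribes a three-group F test; it does not say so. A reader might also infer that EA versus SEA goes untested. That follows only if usual care is the Dunnett reference, which the article does not state, and both SEA and usual care are called controls. Nor is it stated that Dunnett follows the primary ANCOVA, because its sentence comes after the one on repeated measures.

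The allocation-awareness sentence should not be pressed either. It cannot hold for usual care participants, but it sits among text on envelopes and concealment, and the trial is described as assessor-blind.

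The objection does not remove the point. The article goes beyond silence: it states a level, a model and a multiplicity procedure, and together they do not make the sized contrast decide the trial. Several analyses fit the text, and some can declare success with no effect over sham.

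**Conclusion.** The concern holds in limited form. The primary analysis does not fix EA versus SEA as the deciding comparison, and a literal reading allows a positive primary test driven by usual care alone. How often that happens depends on two assumptions: that the group-factor test is the criterion for success, and how far usual care falls behind. The probability is about one in five at 2 points and 83% at 4.15 points. The 4.15 is borrowed from the EA–SEA planning difference, so the whole range should be quoted and not only its upper end.

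The possible double correction is separate. It arises only if Dunnett is run at family-wise 0.025, and then EA–SEA power is about 72% instead of the planned 80%. The sample size itself is correct for one EA–SEA contrast at 0.025.

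**What to change.** 1. State the primary test as the ANCOVA contrast EA minus SEA in ISI change at week 5, and say that a claim of efficacy for EA requires it to be significant.
2. Make EA minus usual care the second contrast, and label it open-label.
3. Do not use a three-group F test as the decision rule.
4. Use one multiplicity method: either Dunnett with EA as the common reference at family-wise 0.05 (EA–SEA power 80.2% at 40 per arm), or the two contrasts at 0.025 each without Dunnett (79.3%).

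This is a change of wording, to be made before unblinding, and 150 participants still suffice. The price is that a win over usual care alone can no longer be reported as efficacy of EA.

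### The primary ANCOVA omits the two factors that stratify the randomisation, so it forgoes some precision if those factors predict ISI change beyond baseline

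*Protocol article*

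**What the plan says.** Under Randomisation, allocation concealment, and blinding, participants are "randomly allocated to one of three groups in a 1:1:1 ratio" by "stratified block randomisation based on whether medications are taken to treat insomnia and the institutions conducting the trial".

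Under Statistical analysis, "The primary outcome measure in this study is the mean change in the ISI from baseline to week 5". The model for it is an "analysis of covariance with baseline as the covariate and the treatment group as the fixed factors", tested two-sided at the 0.025 level. No term for medication use or institution appears there or anywhere else in the article. For the secondary outcomes, the methods "will be the same as those used for the primary assessment analyses". The next sentence assigns chi-square or Fisher's exact tests to categorical data.

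Under Sample size, the EA versus sham comparison is sized at a "two-sided 2.5% significance level and 80% statistical power", with the difference between "EA treatment and SEA control groups as 4.15, and the standard deviation as 6.0". Adjustment for baseline or strata is not mentioned.

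**The concern.** Stratified blocks make the arms alike on medication use and institution. If either factor predicts the outcome, this balance lowers the true variance of the treatment difference. A model without the factors leaves their variance in the residual, so the standard error it reports does not reflect the balance that the design achieved. Confidence intervals are then wider than they need be, and the test rejects less often than its nominal level. The trial takes the trouble to stratify and then does not collect the benefit in the analysis.

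The article states the model's covariate and fixed factor outright. The point therefore concerns a choice that has been made, not a detail left to an analysis plan that is not shown.

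There is some reason to expect the factors to matter. The exclusion criteria bar recent as-needed medication and recent changes to regular medication, so stable users of insomnia medication can enter alongside non-users. Treatment is given at several institutions by unblinded practitioners, and the primary outcome is a patient questionnaire. How strongly either factor predicts the outcome is not documented.

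**Working it through.** **Inputs from the protocol article.** Difference 4.15, SD 6.0, two-sided level 0.025, power 80%, at least 40 per group, 20% dropout, at least 150 in total (Sample size). Model terms are taken from Statistical analysis and stratifiers from the randomisation section.

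**Assumption.** R² is the share of outcome variance, after baseline ISI, that the strata explain. The documents give no value, so 0, 0.05, 0.10 and 0.20 are used. SD 6.0 is treated as the residual SD before the strata are added.

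**Step 1: reproduce the plan's figure.** With critical value 2.2414 and power quantile 0.8416:

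n = 2 × [6.0 × (2.2414 + 0.8416) / 4.15]² = 39.74, rounded up to 40 per group. For dropout, 120 / (1 − 0.20) = 150. Both figures reproduce. At 40 per group the standard error is 6.0 × √(2/40) = 1.342, the standardised difference is 4.15 / 1.342 = 3.093, and power is Φ(3.093 − 2.241) = Φ(0.852) = 80.3%.

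**Step 2: effect of omitting the strata.** Let k = √(1 − R²). Under well-balanced stratified blocks the true standard error is 1.342 × k, while the model without strata still reports about 1.342.

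- Overstatement of the standard error: 1/k
- Actual type I error without strata: 2 × [1 − Φ(2.2414 / k)]
- Power without strata: Φ(0.852 / k)
- Power with strata: Φ(3.093 / k − 2.2414)

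| R² | SE too wide by | Type I error without strata | Power without | Power with |
|---|---|---|---|---|
| 0 | 0% | 0.025 | 80.3% | 80.3% |
| 0.05 | 2.6% | 0.0215 | 80.9% | 82.4% |
| 0.10 | 5.4% | 0.018 | 81.5% | 84.6% |
| 0.20 | 11.8% | 0.012 | 83.0% | 88.8% |

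Example at R² = 0.10: k = 0.9487, type I error = 2 × [1 − Φ(2.363)] = 0.018, power without = Φ(0.898) = 81.5%, and power with = Φ(3.261 − 2.241) = Φ(1.019) = 84.6%.

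**Step 3: check by simulation with t tests.** The normal approximation runs about a point high. With 40 per arm, simulation gives power of about 80%, 80% and 82% without the strata and 81%, 83% and 88% with them, at R² of 0.05, 0.10 and 0.20. Type I error without the strata is about 0.022, 0.018 and 0.012–0.013. Methods differ by a point or so, but the direction does not change.

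**Step 4: allow for imperfect balance.** Take 150 randomised, 20% dropout, blocks of 6, and four centres by two medication strata with 40% on medication (block size, centre number and medication share are assumptions). Type I error without strata is then 0.022, 0.020 and 0.014. Power without against with is 79.6% and 80.3%, 79.1% and 82.1%, and 80.6% and 87.3%.

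**Step 5: the same gain in participants.** Adjustment is worth 40 / (1 − R²) per arm: 42.1, 44.4 and 50.0, or about 2, 4 and 10 extra participants per arm.

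**The case against.** The strongest reply is that nothing is broken. The estimate is unbiased, the error is on the safe side, and 40 per group reproduces from an SD of 6.0 with no adjustment assumed. What is forgone is power above the planned 80%. All of this stands. A reader might infer that the primary p-value is invalid or that the trial is underpowered; the documents support neither.

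The second reply is that the loss is conditional. If the strata explain nothing beyond baseline ISI, the two models agree, and the eligibility rules already narrow the variation in medication. This also stands. At R² = 0.05 the gain is one to two points, and under one point once dropout and incomplete blocks are allowed for. It becomes notable only towards the top of the assumed range.

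The third reply concerns reach. The sentence on secondary outcomes might be read as carrying this model to every one of them. It does not: categorical data get chi-square or Fisher's exact tests, and PGIC has no baseline measurement in Table 2, so a baseline-adjusted ANCOVA cannot apply to it as written. The point is limited to the primary outcome and the continuous secondary outcomes analysed by ANCOVA. The article does not set out terms for the imputation or repeated-measures models, and no finding is made on them.

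Finally, the number and size of institutions are not given, so the cost in degrees of freedom cannot be stated as a figure, and very small institutions need a rule. This is a fair condition on the fix, not a reason against it.

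**Conclusion.** The mismatch between the stratified randomisation and the stated primary model is plain in the text. Its consequence is a possible loss of efficiency, not a threat to validity. For strata explaining 5% to 20% of the variance left after baseline, the reported standard error is about 3% to 12% too wide, the actual type I error falls from 0.025 to between about 0.022 and 0.012, and roughly 1 to 6 points of power are left unused. These sizes rest on an assumed R², on SD 6.0 as the residual SD, and on reasonably balanced strata. This is a free improvement: worth making, but the trial does not depend on it.

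**What to change.** Before unblinding, state the primary model as: change in ISI at week 5 = treatment + baseline ISI + insomnia-medication stratum (yes/no) + institution. Add a rule, fixed in advance, for pooling very small institutions. Use the same stratum terms, with each outcome's own baseline, for the continuous secondary outcomes analysed by ANCOVA.

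The cost is one line of model wording, one degree of freedom for medication, and the number of institutions minus one for institution. Both factors are known for every participant at randomisation, so no new data are needed.
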